### Statistical considerations

#### Sample size estimation

According to the previous works presented in literature, we have estimated that a sample size of 105 patients per randomized group would provide 95% statistical power of highlighting an effect-size greater than 0.5 for a two-sided type I error at 5% for the primary outcome GAS T-score. Finally, a total of 250 patients (125 by group) will be considered to take into account lost to follow-up. With such sample size, a minimal absolute difference of 20% (50% versus 30%) can be shown for the secondary endpoint clinical improvement as defined in the thermarthrose [13] study for a power of 90%.

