#### Statistical analysis

Statistical analyses will be conducted using the Stata software (version 13, StataCorp, College Station, USA). A two-sided *p*-value of less than 5% will be considered to indicate statistical significance.

Concerning the primary outcome, the comparison between groups for univariate analysis will be analyzed using Student’s *t*-test or Mann-Whitney’s test. The normality will be studied by the Shapiro-Wilk test and the homoscedasticity using the Fisher-Snedecor test. Then, the analysis of the primary outcome will be completed by multivariable analysis using a linear mixed model to take into account: (1) fixed effects covariates determined according to univariate results and to clinical relevance (for example gender, age, analgesic treatments and season) and (2) center as random-effects (to measure between and within center variability). The normality of residuals will be studied as aforementioned. Intention-to-treat (ITT) analysis will be considered for the primary outcome, more precisely for all randomized patients except those without consent.

Other continuous endpoints (WOMAC, HEIQ, pain VAS, quality of life SF36, BMI) will be studied using the same statistical plan whereas the categorical parameters will be compared between groups with chi-squared or Fisher’s exact tests in univariate analyses and using generalized linear mixed model for multivariable analyses. For HEIQ and SF36 scores and pain VAS, the comparisons between groups will include in multivariable analyses the baseline values as independent parameters (fixed effects) as suggested by Vickers and Altman [18].

Longitudinal analyses concerning repeated measures at day 18 and months 3, 6, and 12 will be studied using random-effect models (linear or generalized linear), to take into account patient as random-effect (slope and intercept), nestled in center random-effect, while studying the fixed effects: group, time, and interaction *group x time*. According to clinical relevance, sub-group analyses depending the gender will be proposed after the analysis of interaction sub-group x randomization group in regression models (for repeated data or not).

Secondarily, a per-protocol analysis will be considered. A particular attention will be paid on number and duration of sessions and the type of intervention.

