Finally, a sensitivity analysis will be performed and the nature of missing data will be studied (missing at random or not). According to this, the most appropriate approach to the imputation of missing data will be proposed (maximum bias (e.g., last observation carried forward vs. baseline observation carried forward) or estimation proposed by Verbeke and Molenberghs for repeated data).

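### The imputation method hangs on deciding whether data are missing at random, which observed data cannot show, so the choice for the 6-month GAS is left until after the data are seen

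*Protocol article*

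**What the plan says.** Missing data are covered in the closing paragraph of Statistical analysis. It sets out two steps. First, alongside a sensitivity analysis, "the nature of missing data will be studied (missing at random or not". Second, "According to this, the most appropriate approach to the imputation of missing data will be proposed".

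Two routes are offered. One is described as "maximum bias (e.g., last observation carried forward vs. baseline observation carried forward". The other is "or estimation proposed by Verbeke and Molenberghs for repeated data".

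Three other statements bear on this:

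- Earlier in the same section, an intention-to-treat "analysis will be considered for the primary outcome, more precisely for all randomized patients except those without consent".
- Sample size estimation expects losses: "a total of 250 patients (125 by group) will be considered to take into account lost to follow-up", against 105 per group needed for the stated power.
- Primary outcomes places the GAS at 6 months and scores it from -2 to +2, with 0 as the expected level. It defines no baseline GAS level and mentions no GAS scoring before month 6. Statistical analysis refers to repeated measures at day 18 and months 3, 6 and 12, without saying whether the GAS is one of them.

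**The concern.** The difference between MAR and MNAR concerns the values that were not observed, given those that were. Baseline comparisons of completers and dropouts can show that data are not missing completely at random, but they cannot show which of the other two holds. A rule that makes the method follow from that finding has no valid input. What remains is a choice made with the data in hand, among methods that can give different treatment effects.

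The first route has its own problem. LOCF and BOCF each put a fixed kind of value into both arms by the same rule. That does not produce the two extremes of the treatment effect. When retention differs by arm, which is plausible where participants know whether they attend workshops, the imputed values convert the retention difference into a GAS difference.

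**Working it through.** **Inputs from the document.** Effect size 0.5, two-sided 5%, 95% power, 105 evaluable and 125 randomised per group; GAS levels -2 to +2.

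**Assumptions, not in the document.** T-score SD of 10 (so effect size 0.5 is 5 points); loss rates by arm; the baseline GAS level; the 6-month mean; within each arm, loss unrelated to the score in steps 3 to 5.

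**1. The plan's own figure.** n = 2(1.960 + 1.645)² / 0.5² = 104 per group by the normal formula; the t-test version gives 104.93, so 105. This reproduces. The loss allowance implied is 1 - 105/125 = 16%; the rate itself is not stated.

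**2. Why studying the mechanism cannot choose the method.** Let missing patients in the intervention arm differ from observed ones by s, with no such shift in the control arm. With 16% missing per arm and an observed difference of 5 T-score points, the difference over all randomised patients is 5 + 0.16 × s:

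| s | Difference |
|---|---|
| 0 (MAR) | 5.0 |
| -10 (MNAR) | 5 - 1.6 = 3.4 |
| -20 (MNAR) | 5 - 3.2 = 1.8 |

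All three rows fit the same observed data. Holding the completers' standard error at 10 × √(2/105) = 1.38, significance is lost at s = (1.96 × 1.38 - 5)/0.16, about -14.3 points. The assumption matters, and the data do not reveal it.

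**3. LOCF and BOCF are not bounds.** With equal loss and no true effect, BOCF moves the group difference by zero. Opposed extremes at 16% loss (+2 in one arm, -2 in the other) move it by 0.16 × 2 + 0.16 × 2 = 0.64 levels relative to imputing 0 in both.

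**4. Unequal loss becomes effect.** With no true effect and a common 6-month mean μ, filling in a value with mean b gives an expected difference of (difference in loss) × (μ - b). This applies to BOCF with b the baseline level, and to LOCF with b the mean of the last earlier score. Take BOCF, μ = 0, SD 1, 125 per group, loss 10% versus 22%:

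- b = -2: 0.12 × 2 = 0.24 levels. Variances are 0.90 + 0.90 × 0.10 × 4 = 1.26 and 0.78 + 0.78 × 0.22 × 4 = 1.466; SE = √(2.726/125) = 0.148; z = 1.63; rejection about 37%.
- b = -1: 0.12 × 1 = 0.12 levels. Variances are 0.99 and 0.952; SE = √(1.942/125) = 0.125; z = 0.96; rejection about 16%.

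A simulation of 4,000 trials per setting with a five-level score of SD about 1 gave 0.241 levels and 36.4%, and 0.120 levels and 16.7%.

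**5. The same on the T-score.** BOCF at T = 40 or 30, control mean 45 or 50:

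| Loss (intervention / control) | True difference | BOCF result |
|---|---|---|
| 16% / 16% | 0 | no bias, type I error about 5% |
| 16% / 16% | 5 | 0.84 × 5 = 4.2; power 76-93%, against about 95% for available cases |
| 8% / 24% | 0 | false difference 0.8 to 3.2; type I error about 10-58% |
| 8% / 24% | 5 | 5.4 to 7.8 |
| 24% / 8% | 5 | 0.6 to 3.0 |

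The bias can go either way, and its size depends on loss by arm and on the baseline level.

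**6. Are the named options usable for the primary outcome?** BOCF needs a baseline GAS level, and none is defined. LOCF needs an earlier GAS score, and the repeated-data estimation needs several; neither is stated to exist. If the GAS is scored only at month 6, none of the three works as written.

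**The case against.** The strongest reply has four parts.

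*The paragraph opens with a sensitivity analysis and labels LOCF against BOCF as a maximum-bias approach.* This is fair. A reader might infer that LOCF or BOCF is the primary method, so that the false-positive rates above belong to the trial's main test. The text does not commit to that. Even as a stress test, though, the pair does not do what its label says (step 3).

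*A principled option is also named.* The repeated-data estimation is sound in kind, and the section already plans random-effects models. But it is reached through the same unworkable step, and it needs repeated GAS scores.

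*This is detail for an analysis plan, and the data analysts are to be blinded.* Leaving the imputation model to the SAP would be no finding. Here the article states a rule, and a SAP that followed it would inherit the fault. Blinding limits the concern about a choice made after seeing the data, but does not remove it.

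*Some stronger readings go beyond the text.* A reader might infer that the t-test or Mann-Whitney test uses only patients with a 6-month score and so contradicts intention-to-treat. The document does not say so; imputation is mentioned, and how these patients enter the primary analysis is simply not fixed. Nor does it say that LOCF would carry an end-of-spa score, that BOCF would place every lost patient below the expected level, or that a formal test of mechanism will be run.

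**Conclusion.** The concern holds for the selection rule. Choosing the imputation by whether data are missing at random cannot be carried out, and it leaves an open choice after the data are seen. That conclusion needs no assumption beyond the wording of Statistical analysis.

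It holds conditionally for LOCF and BOCF. Applied alike in both arms they do not bound the bias, and they distort the comparison when loss differs by arm. The figures (0.24 or 0.12 levels; about 36% or 17% false positives) illustrate one assumed loss split and two assumed baseline levels. They are not a forecast for this trial. With equal loss and no true effect there is no bias; with equal loss and a true effect, BOCF shrinks it. The sample size is unaffected. This should be corrected before the data are analysed.

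**What to change.** In Statistical analysis and in the SAP:

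1. State when the GAS is scored and whether a baseline level exists.
2. Prespecify one primary method under MAR for the 6-month GAS, covering every randomised patient with consent. Either use multiple imputation by arm with centre, baseline covariates and any earlier scores or, if the GAS is scored repeatedly, a likelihood-based mixed model on those scores.
3. Add delta-adjusted imputation with arm-specific shifts, taken to the tipping point, as the MNAR sensitivity analysis.
4. Remove the choice of method by mechanism, and remove LOCF and BOCF. Describing the pattern of and reasons for missing data by arm can stay, as description only.

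The cost is wording and a little programming. No new data are needed, and the sample size does not change.

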#### Ethics

All patients will receive verbal and written information on the aim of the study and the protocol. Written informed consent will be obtained prior to their inclusion in the study and before performing any specific procedure. During the study, patient will have the opportunity to ask all questions concerning the protocol to the investigator. They will be informed that they are free to stop the study at any time at their own discretion, in accordance with the Good Clinical Practice in current enforced under the French regulatory framework. Consent form is available from the corresponding author on request.

Any adverse event or serious adverse event that could occur during the protocol will be reported to the DMC and relevant regulatory bodies indicating expectedness, seriousness, severity, and causality. Should there be any negative impact of participating in the study on the patient’s health status, the participant will be entitled to compensation in accordance with the French regulations.

Pursuant to the provisions concerning the confidentiality of data that are available to persons responsible for quality control of biomedical research, persons with direct access will take all necessary precautions to ensure the confidentiality of information (identity and patients results). Data collected will be made anonymous.

Any changes in the protocol will be notified to the AFRETH then the primary investigator will notify the centers. A copy of the revised protocol will be sent to the primary investigator to add to the Investigator Site File. Any deviations from the protocol will be fully documented using a breach report form and will update the protocol in the Clinical Trials website.

On the consent form, participants will be asked if they agree to use of their data should they choose to withdraw from the trial. Participants will also be asked for permission for the research team to share relevant data with people from the universities taking part in the research or from regulatory authorities, where relevant. This trial does not involve collecting biological specimens for storage.

#### Patient and public involvement

Patients were not involved in the development and the design of the study. The burden of the intervention will not be assessed by patients themselves. Patients will receive a written summary of tests and evaluation results they will have completed during their rehabilitation and will be written informed of global study results at its end.

#### Management of the study

Data will be collected and managed using REDCap (Research Electronic Data Capture) electronic data capture tools hosted at the University Hospital of Clermont-Ferrand. REDCap is a secure, web-based application designed to support data capture for research studies, providing:An intuitive interface for validated data entry;Audit trails for tracking data manipulation and export procedures;Automated export procedures for seamless data downloads to common statistical packages;Procedures for importing data from external sources.

A clinical research assistant will be commissioned to ensure that the progress of the study and the data are captured according to the Standard Operating Procedures implemented at the University Hospital of Clermont-Ferrand.

The trial steering committee consists of the sponsor, the investigator, and the researcher responsible for the study. The trial steering committee meets every second month to ensure that the trial conforms to the protocol and are also available to the clinicians for day to day support and questions regarding the trial and participants. Additionally, two professors, who are independent from the data collection, are continuously supervising the trial with yearly meetings with the trial steering committee and will supervise the data analysis and interpretation of data.

[name] and the nurses in charge of the study will be responsible for all aspects of local organization including identifying potential recruits and taking consent.

#### Data monitoring

Quality control and quality assurance follows regular procedures. The internal monitoring team are independent from the intervention and have no competing interests. When a participant is recruited and obtains written informed consent, the monitoring team afterwards check that it is filled out correctly.

An interim analyses will be provided in case of insufficient recruitment of the study and if needed stopping the trial.

## Discussion

OA is a high-prevalence disease, whose prevalence will increase in the future [19]. Treatments will be based on modifiable risk factors, such as pain, function, obesity, comorbidities, intrinsic barriers to PA practice, and sedentary time by the real modification of the lifestyle of the patients [20, 21].

This randomized trial will be the first study to compare the effect of a self-management workshops associated with spa therapy versus spa therapy alone. The efficacy of spa therapy in knee OA has been demonstrated, with good level of evidence for pain and disability [22], but the effect of an additional self-management workshops is unknown. Our study would be the first to evaluate it and the main outcome will be measured by Goal Attainment Scaling (GAS).

Measurement through Goal Attainment Scaling (GAS) apply in many other areas including chronic pain [23], elderly care settings [24, 25], cognitive rehabilitation [26], and amputee rehabilitation [27]. GAS offers a number of potential advantages as an outcome measure. This goal-setting builds on already established process to encourage communication and collaboration between the multi-disciplinary team members as they meet together for goal-setting and scoring patient involvement—there is emerging evidence that goals are more likely to be achieved if patients are involved in setting them. Moreover, there is also evidence that GAS has positive therapeutic value in encouraging the patients to reach their goals [28].

In spite of the limitation, assessing the effectiveness of non-pharmacological treatments such as behavioral therapy the blinding of participants and care providers is frequently impossible; the success of the treatment often depends on the skill and experience of care providers. As an outcome measure, there is growing evidence for the sensitivity of GAS over standard measures [29]. It potentially avoids some of the problems of standardized measures including floor and ceiling effects and lack of sensitivity—particularly of global measures, where individuals make change in one or two important items, but this change is lost in the overall scores, where a large number of irrelevant items do not change [29]. One of the most attractive advantage of GAS is its individualized approach to evaluation.

The findings of this trial could offer new perspectives in establishing best clinical practice guidelines for this patient population.

## Trial status

The randomization of patients commenced in March 2019 and is ongoing till December 2023. Protocol Version: 6 – 12 March 2018.

## Data Availability

The datasets analyzed during the current study and statistical code are available from the corresponding author on reasonable request, as is the full protocol.
